### The «COGNITUS & MOI» program

The «COGNITUS & MOI» program is a cognitive remediation tool, specifically for children, and is dedicated to attentional and visuospatial functions. A precise description of the program has been previously published [25]. Briefly, it is based on the following four main principles:targeting daily life difficulties with concrete objectives;adjusting activities to the individual child’s cognitive profile and rate of progression;encouraging the use and transfer of strategies while facing cognitive difficulties; anda coaching approach leading to an interactive process between the therapist, child and his or her parents.

During the program, the therapist resorts to strategies or attitudes such as temporal structuration, verbal mediation, positive reinforcement and above all metacognitive questioning.

The present protocol includes 17 meetings with a therapist that has been specifically trained in the «COGNITUS & MOI» program. The first preliminary session will apply to the child and their parents. The therapist will do the following:go through the behavioral, neurocognitive and functional assessment and outline the strengths and weaknesses of the child’s cognitive profile.provide psychoeducation by explaining to the child and their parents what attentional and visuospatial functions are and their implications in daily life. In particular, this is achieved through a comic strip given to the child and a brochure with written information given to the parents.define with the child and his parents the concrete aims of the therapy in accordance with his cognitive profile and difficulties in daily life.introduce the program.explain the role of at-home activities in strategy transfer and provide the child with the «COGNITUS & MOI» book (a child-friendly notebook that holds reports of at-home activities).

Each of the following 16 weekly sessions will last 1 hour and be identically structured. Each session begins with the program description and a review of the at-home activity for the previous week. The paper-and-pencil activities and computerized activities occur next and take 15 min each. The therapist creates paper-and-pencil activities on a case-by-case basis depending on the child’s cognitive profile and hobbies. The therapist chooses computerized activities from the exercises in the attentional and visuospatial modules. Each session ends with a Cognitus’ facial expression recognition task and an explanation of the at-home activity to the child and their parents.

### The motor skill and video viewing intervention

The motor skill and video viewing intervention is structured in a similar manner as the «COGNITUS & MOI» program but does not follow the same key principles. Activities are fixed in advance and are not adjusted to the child’s profile. Concrete objectives are not defined, and use of strategy is not encouraged. The therapist does not provide coaching except for positive reinforcement and temporal structuration of the sessions.

During the first session, the therapist will only explain the results of the assessment, introduce the program and provide the child with a child-friendly notebook that holds at-home activity reports.

The 16 weekly sessions will be structured in the same manner as the «COGNITUS & MOI» program except that there will be no facial expression recognition task. The therapist will adjust the paper-and-pencil activities for difficulties but will conform to a specific order with regard to the fine motor functions that are taught in each session (spreading, tying, blowing, nailing, pouring, coloring, screwing, etc.). The computerized activities consist of passive viewing of videos that are appropriate for the child’s age.

### Assessments and outcomes

Assessments will include behavioral problems, neurocognitive abilities (language, memory, praxis and visuospatial abilities and attentional and executive functions), social cognitive processes (emotion recognition and theory of mind abilities) and functional outcome (quality of life, self-esteem and adaptive and daily living skills) measures. Assessments will involve the child, their parents and an experienced psychologist.

The primary outcome is the change from the baseline of the score on the “hyperactivity – noncompliance” subscale of the Aberrant Behavior Checklist [26].

Secondary outcomes are as follows:the change from the baseline of the scores for a semi-structured interview investigating adaptive behaviors and daily living skills,the change from the baseline of the scores of two questionnaires investigating quality of life and self-esteem,the change from the baseline of scores of paper-and-pencil subtests, computerized subtests and questionnaires investigating praxis and visuospatial functions, memory, language, attentional and executive functions, and social cognition, andthe change of all scores from post-treatment to the 6-month follow up.

See Table 2 for a detailed overview of the assessments and outcome measures.

**Table 2 Tab2:** Measurements

	Kind of measure	Name	type	informant	recruitment	baseline assessment	post-treatment assessment	6-months follow up assessment
	IQ estimation	WPPSI-III, WPPSI-IV, WISC-IV or WISC-V	P&P	C	*			
*primary outcome*	behavioural problems	ABC	Q	P	*	*	*	*
*secondary outcome*	adaptive and daily living skills	VABS-II	S Int.	P	*	*	*	*
	quality of life	KIDSCREEN-27	Q	P		*	*	*
	self esteem	self-esteem subscale MDI-C	Q	C		*	*	*
	lexical knowledge	PPVT	P&P	C		*	*	*
	learning and long term memory	word list CMS	P&P	C		*	*	*
		dot locations CMS	P&P	C		*	*	*
	praxis and visuospatial functions	visuomotor precision NEPSY-II	P&P	C		*	*	*
		imitating hand positions NEPSY-II	P&P	C		*	*	*
		arrows NEPSY-II	P&P	C		*	*	*
		block construction NEPSY-II	P&P	C		*	*	*
		route finding NEPSY-II	P&P	C		*	*	*
	attentional functions	sky search TEA-Ch	P&P	C		*	*	*
		alertness TAP 2.3	CT	C		*	*	*
		auditory attention NEPSY-II	P&P	C		*	*	*
		divided attention TAP 2.3	CT	C		*	*	*
	executive functions	Go/NoGo TAP 2.3	CT	C		*	*	*
		response set NEPSY-II	P&P	C		*	*	*
		inhibition NEPSY-II	P&P	C		*	*	*
		mazes WISC-III	P&P	C		*	*	*
	social cognition	affect recognition NEPSY-II	P&P	C		*	*	*
		theory of mind NEPSY-II	P&P	C		*	*	*
		EQS	Q	P		*	*	*

*WPPSI* Wechsler Preschool and Primary Scale of Intelligence (Wechsler, 2004; 2014), *WISC* Wechsler Intelligence Scale for Children (Wechsler, 2005; 2016), *ABC* Aberrant Behavior Checklist (Aman & Singh, 1986), *VABS-II* Vineland Adaptive Behavior Scales – Second Edition (Sparrow, Cicchetti, & Balla, 2015), *KIDSCREEN-27* (Robitail et al., 2007), *MDI-C* multiscore Depression Inventory for Children (Berndt & Kaiser, 1999), *PPVT* Peabody Picture Vocabulary Test (Dunn, Thériault-Whalen, & Dunn, 1993), CMS Children’s Memory Scale (Cohen, 2001), *NEPSY-II* Developmental NEuroPSYchological Assessment – Second Edition (Korkman, Kirk, & Kemp, 2012), *TEA-Ch* Test of Everyday Attention for Children (Manly, Robertson, Anderson, & Mimmo-Smith, 2004), *TAP 2.3*. Test of Attentional Performance – Version 2.3 (Zimmermann & Fimm, 2012), *WISC-III* Wechsler Intelligence Scale for Children - Third Edition (Wechsler, 1996), *EQS* Empathy Quotient Questionnaire (Baron-Cohen & Wheelwright, 2004); *P&P* paper and pencil test; *Q* questionnaire; *S* Int. semi structured interview; *CT* computerized test; *C* child; *P* parents

### Sample size

To our knowledge, only one previous study has evaluated the effectiveness of a non-drug treatment using the “hyperactivity – noncompliance” score of the ABC as the primary outcome measurement [27]. A decrease of 3 points after treatment was found to be significant (M = 12.1; SD = 8.9 versus M = 9; SD = 7.4). Therefore, we hypothesize that following the motor skills and video viewing intervention, we will observe a 3 point decrease of the “hyperactivity – noncompliance” score. We expect that the decrease will be double for the «COGNITUS & MOI» program: the difference between the two treatments would be at least 3 points. With an expected SD of 5, a power of 90%, 1:1 allocation into the two groups, two-sided testing and a significance level of 5%, a total sample of 126 participants is required. Given the insufficient information from the literature and the risk of dropout, 200 participants will be enrolled in the present study.

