### Statistical analysis

Descriptive statistics will be reported for each variable of interest for the two groups.

First, independent-sample t-tests or non-parametric Mann-Whitney tests will be run to assess the lack of differences between groups in age, IQ or severity of ABC scores at baseline (*p* < 0.05, two-sided).

Second, independent-sample t-tests or non-parametric Mann-Whitney tests will be run to compare the “hyperactivity – noncompliance” score change from the baseline to post-treatment assessment in the two groups (*p* < 0.05, two-sided).

Third, similar tests will be run for each secondary outcome measure. The score changes will be separately considered from the baseline to post-treatment assessment and from the post-treatment to 6-month follow-up assessment (*p* < 0.05, two-sided).

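### The planning SD of 5 is unsourced and well below the only SDs cited (8.9 and 7.4), so the 90% power rests on an unstated pre-post correlation of about 0.83

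*Protocol article*

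**What the plan says.** The Sample size section of the protocol article relies on one earlier non-drug study that used the same subscale as its primary measure. It reports that study's result as "M = 12.1; SD = 8.9 versus M = 9; SD = 7.4". It then sets the target for this trial: "the difference between the two treatments would be at least 3 points". The remaining inputs come in one sentence: "With an expected SD of 5, a power of 90%, 1:1 allocation into the two groups, two-sided testing and a significance level of 5" per cent. The stated requirement is 126 in total. The section ends: "Given the insufficient information from the literature and the risk of dropout, 200 participants will be enrolled in the present study".

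Two other sections fix the scale on which the SD is needed. Under Assessments and outcomes: "The primary outcome is the change from the baseline of the score on the" hyperactivity–noncompliance subscale. Under Statistical analysis: "Second, independent-sample t-tests or non-parametric Mann-Whitney tests will be run to compare the" change in that score from baseline to post-treatment between the groups. No adjustment for the baseline score is planned.

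**The concern.** The test is an unadjusted two-group comparison of change, so power depends on the SD of the change. The article plans on 5 without saying whether this is the SD of a score or of a change, where it comes from, or what pre-post correlation it implies. Both SDs printed two sentences earlier are much larger.

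Required sample size grows with the square of the SD, so the choice matters. The increase from 126 to 200 has to cover both uncertainty in the literature and dropout. Neither is quantified, so the reader cannot tell how large an SD the trial can tolerate. If the SD of change is well above 5, a non-significant result would come from a trial with less power than the paragraph suggests.

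**Working it through.** **Inputs from the article.** Difference 3; SD 5; two-sided 5%; power 90%; 1:1; N = 126, enrolled 200 (Sample size). Cited SDs 8.9 and 7.4 (same section). Outcome and test on change from baseline (Assessments and outcomes; Statistical analysis).

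**Assumptions, not in the article.** The cited SDs are pre- and post-treatment SDs of the score, as their position beside the two means suggests. The pre-post correlation r is varied from 0.5 to 0.8. Loss is set at 15% (170 analysed) or 20% (160 analysed) for illustration. The 3-point difference is taken as given.

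**Step 1: reproduce 126.** Standardised difference 3/5 = 0.6.
- Normal approximation: 2 × (1.960 + 1.282)² × 25/9 = 58.4, so 59 per group and 118 in total.
- Exact t-test: 59.35, so 60 per group and 120 in total.
- Mann-Whitney allowance: 59.35/0.955 = 62.15, so 63 per group and **126** in total.

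The stated figure is reproduced, and the Statistical analysis section does allow a Mann-Whitney test. The t-test power with 63 per group is 91.6%.

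**Step 2: correlation implied by SD 5.** SD of change = √(8.9² + 7.4² − 2r × 8.9 × 7.4) = √(133.97 − 131.72r). Setting this to 5 gives r = (133.97 − 25)/131.72 = **0.83**.

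**Step 3: power of the planned comparison** (t-test on change, difference 3).

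| Assumed r | SD of change | Power, 126 | Power, 170 | Power, 200 | N for 90% |
|---|---|---|---|---|---|
| 0.5 | 8.25 | 53% | 65% | 72.5% | 322 |
| 0.6 | 7.41 | 62% | 75% | 81% | 260 |
| 0.7 | 6.46 | 73% | 85% | 90% | 198 |
| 0.8 | 5.35 | 88% | 95% | 98% | 136 |
| 0.83 | 5.00 | 92% | 97% | 99% | 120 |

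**Step 4: largest change SD that keeps 90% power.**
- 126 analysed: 5.15 (r at least 0.82).
- 160 analysed: 5.82 (r at least 0.76).
- 170 analysed: 6.0 (r at least 0.74).
- 200 analysed: 6.51 (r at least 0.70).

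With 200 analysed, 80% power holds up to 7.54 (r at least 0.59).

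**Step 5: the other reading.** If 5 was meant as the SD of a score, the direct comparison is with the cited score SDs. SD 7.4 would give 62% power at 126 and 81% at 200; SD 8.9 would give 47% and 66%.

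**Step 6: baseline-adjusted analysis of the same data.** Residual SD = 7.4 × √(1 − r²). This assumes a post-treatment SD of 7.4 and a common slope in both groups.

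| Assumed r | Residual SD | Power, 170 | Power, 200 |
|---|---|---|---|
| 0.5 | 7.4 × √0.75 = 6.41 | 86% | 91% |
| 0.6 | 7.4 × √0.64 = 5.92 | 91% | 95% |
| 0.7 | 7.4 × √0.51 = 5.28 | 96% | 98% |
| 0.8 | 7.4 × √0.36 = 4.44 | 99% | over 99% |

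**The case against.** A reader might infer that 5 contradicts 8.9 and 7.4. The article does not support that. The cited values stand beside two means and are SDs of scores, while the outcome is a change. The SD of a change can be below both score SDs when the correlation is high, and Step 2 shows that 5 is attainable.

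A reader might also infer that 126 is a miscalculation. It is not: the statement is conditional on SD 5, and the number follows from the stated inputs.

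Nor can one say from this document that a correlation of 0.83 is implausible. The article gives no correlation at all, so nothing in it makes 0.5 more likely than 0.8. At r = 0.8 the trial has 95% power with 170 analysed and 98% with 200.

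The strongest defence is that 126 is not the trial size. The article admits that the literature is insufficient and enrols 59% more (200/126 = 1.59), partly for that reason. It never claims 90% power for 200 under a larger SD. The full protocol may also explain where the 5 came from.

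These points rule out any charge of contradiction or arithmetic error, and they lower the severity. They do not supply a definition or a basis for the SD. The hedge also has to absorb dropout of unstated size. The article itself foresees discontinuation for aggravation, refusal or repeated absence (Inclusion and exclusion criteria) and questions attendance (Discussion).

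**Conclusion.** The point holds as one of justification: the 90% power depends on an SD that is undefined, unsourced and well below the only SDs cited. At 126 there is almost no tolerance, since 90% is lost once the change SD exceeds about 5.15. At 200 there is real but limited tolerance: up to about 6.5 with no loss, and about 6.0 with an assumed 15% loss. Over the assumed r of 0.5 to 0.8, power at 200 runs from 72.5% to 98%, so the trial may be well powered or clearly short of 90%, and the article does not let the reader judge which.

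These results rest on reading 8.9 and 7.4 as pre and post SDs, on their carrying over to this population, and on the assumed correlations and losses. They do not show that the trial is underpowered or that more children are needed. Should fix.

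**What to change.** Keep enrolment at 200 and make two changes.

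1. **Sample size.** State that 5 is the SD of the change, with its source or the correlation it implies (about 0.83 from the cited SDs). Replace the power statement at 126 with the power at 200, and at 200 less an explicit dropout rate, over change SDs from 5 to 8.25 (r from about 0.83 down to 0.5).
2. **Statistical analysis.** Replace the unadjusted test of change with a baseline-adjusted comparison as the primary analysis: ANCOVA with the baseline hyperactivity–noncompliance score as covariate. Base the stated power on that model. Change can remain the reported outcome, because adjusting change or the post-treatment score for baseline gives the same treatment difference.

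The two changes belong together: quoting adjusted power while keeping an unadjusted test would create a new mismatch.

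The cost is a rewritten sample-size paragraph and an amended primary analysis, made before outcome data are examined. No extra children or measurements are needed, since the baseline score is already collected. The power table will include less favourable values. In return, at r = 0.5 power rises from 72.5% to about 91% with 200 analysed, and from 65% to about 86% with 170.

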### Statistical analysis

Descriptive statistics will be reported for each variable of interest for the two groups.

First, independent-sample t-tests or non-parametric Mann-Whitney tests will be run to assess the lack of differences between groups in age, IQ or severity of ABC scores at baseline (*p* < 0.05, two-sided).

Second, independent-sample t-tests or non-parametric Mann-Whitney tests will be run to compare the “hyperactivity – noncompliance” score change from the baseline to post-treatment assessment in the two groups (*p* < 0.05, two-sided).

Third, similar tests will be run for each secondary outcome measure. The score changes will be separately considered from the baseline to post-treatment assessment and from the post-treatment to 6-month follow-up assessment (*p* < 0.05, two-sided).

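### The primary comparison of unadjusted change scores is valid but less precise than baseline-adjusted ANCOVA, and naming two tests leaves the deciding p-value open

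*Protocol article*

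**What the plan says.** The Assessments and outcomes section defines the endpoint: "The primary outcome is the change from the baseline of the score on the" hyperactivity–noncompliance subscale of the ABC. The Statistical analysis section then states "Second, independent-sample t-tests or non-parametric Mann-Whitney tests will be run to compare the" "score change from the baseline to post-treatment assessment in the two groups", two-sided at 0.05. It extends similar tests to every secondary outcome, taking baseline to post-treatment and post-treatment to six months as separate intervals.

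The primary comparison has no covariates. The Randomization section forms four strata from age (6–9, 10–13) and IQ (45–55, 56–70), but these do not enter the comparison. Age, IQ and baseline ABC severity are used only in significance tests of baseline balance, with no stated consequence.

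The Sample size section assumes that "the difference between the two treatments would be at least 3 points" and continues "With an expected SD of 5, a power of 90%, 1:1 allocation into the two groups", which leads to 126 required and 200 enrolled. It does not say whether the SD of 5 belongs to the change or to the score, or which test was sized. The cited study's before and after values are given as "M = 12.1; SD = 8.9 versus M = 9; SD = 7.4".

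**The concern.** Subtracting the baseline is the same as adjusting for it with a slope of exactly 1. When the score is imperfectly reproducible, the slope that minimises the variance is below 1, so the change score carries avoidable noise. The data needed to do better are already collected, and the two stratification factors are known for every child.

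Separately, the t-test and the Mann-Whitney test answer different questions, a mean difference and a stochastic ordering. The sample size is built on a 3-point mean difference, which the Mann-Whitney test does not estimate. Naming both without saying which decides leaves two candidate p-values for the main result. At stake are precision, which matters if the SD of 5 proves too small, and a primary result that is not tied to one number.

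**Working it through.** **Inputs.** From the Sample size section: difference 3, SD 5, two-sided 5%, power 90%, 126 required, 200 enrolled; cited-study SDs 8.9 and 7.4. Assumed, because the article does not give it: the correlation r between baseline and post-treatment scores, shown at 0.5, 0.7 and 0.83.

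**1. The plan's own figure.** Normal approximation: n per arm = 2 × [5 × (1.960 + 1.282)/3]² = 58.4, so 59 per arm, 118 in total. The exact t-test needs 60 per arm, 120 in total. Dividing 60 by the Mann-Whitney efficiency under normality, 3/π = 0.955, gives 62.8, so 63 per arm and 126 in total. That matches, but so does 120 × 1.05 = 126, so the figure does not settle which test was sized.

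**2. Variance with equal baseline and post-treatment variances.** Change: 2σ²(1 − r). ANCOVA residual: σ²(1 − r²). Ratio: (1 + r)/2.
- r = 0.5: 0.75, a 25% reduction
- r = 0.7: 0.85, a 15% reduction
- r = 0.83: 0.915, about a 9% reduction

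**3. Variance with the cited study's SDs.** Change: 8.9² + 7.4² − 2r × 8.9 × 7.4 = 133.97 − 131.72r. ANCOVA: 7.4²(1 − r²) = 54.76(1 − r²). The best slope is r × 7.4/8.9. The r at which these SDs give a change SD of 5 is (133.97 − 25)/131.72 = 0.83.

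| r | best slope | change variance (SD) | ANCOVA variance (SD) | ratio |
|---|---|---|---|---|
| 0.5 | 0.42 | 68.1 (8.25) | 41.1 (6.41) | 0.60 |
| 0.7 | 0.58 | 41.8 (6.46) | 27.9 (5.28) | 0.67 |
| 0.83 | 0.69 | 25.0 (5.00) | 17.3 (4.16) | 0.69 |

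**4. Power for 3 points, 100 per arm analysed.** Power ≈ Φ(3/(SD × √(2/100)) − 1.96).
- Change SD 5: 3/0.707 = 4.24, power about 99%; with ANCOVA also above 99%.
- Cited SDs, r = 0.5: unadjusted 3/1.167 = 2.57, about 73% (72.5% by exact t-test); ANCOVA 3/0.906 = 3.31, about 91%.
- Cited SDs, r = 0.7: unadjusted 3/0.914 = 3.28, about 90–91%; ANCOVA 3/0.747 = 4.01, about 98%.

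If only 126 are analysed, with change SD 5 and equal variances, power is 92.0% unadjusted against 97.3% (r = 0.5) or 95.5% (r = 0.7) with ANCOVA.

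None of these figures includes any gain from the age and IQ strata, for which the article gives no basis.

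**5. Two tests.** Null simulation, 40,000 trials per setting, 63 or 100 per arm. Each test alone rejects in about 5% of trials. Rejecting when either is significant gives 5.9–6.1% (normal), 6.6–6.9% (heavy tails) and about 7.2% (strong skew). The tests disagree at the 5% level in about 2% of null trials with normal data, about 4% with skewed data, and about 7% of trials when the true difference is 1.5 points (SD 5).

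**The case against.** The strongest reply is that nothing here is invalid. In a randomised trial a t-test of change is unbiased and holds its level, and it matches the endpoint as defined. A reader might infer that chance baseline imbalance biases the result. It does not: with SD 8.9 and 100 per arm, the baseline difference has standard error 8.9 × √(2/100) = 1.26 points, and its effect on the contrast is already inside the test's standard error. A reader might also say that baseline is discarded; it is used, with its slope fixed at 1.

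Nor does the text show that the trial is underpowered. The SD that the plan adopts is 5; 8.9 and 7.4 are raw-score SDs from one cited study, and the 72% figure needs those SDs together with an assumed r of 0.5. At the r that reproduces an SD of 5, the unadjusted test already has about 99% power with 200 analysed. The larger variance savings also rely on the post-treatment SD shrinking here as it did in that study.

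On the two tests, the ordinary reading is a choice by distribution, and the rule may sit in an analysis plan that is not shown. A simulated normality check followed by the matching test (100 per arm, 8,000 null trials) gave 5.2%, 5.4% and 4.7% for normal, heavy-tailed and skewed data, close to nominal. So it cannot be said that the plan inflates type I error.

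All of this stands. It limits the point to efficiency and to tying the result to one test. It does not answer why available precision should be left unused.

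**Conclusion.** The point holds as a free improvement to a valid analysis. The unadjusted change score costs about 9% to 25% in variance under equal variances, or about 31% to 40% under the cited SDs, for assumed r between 0.83 and 0.5. If the change SD is 5 and all 200 are analysed, the loss has almost no effect on power. It matters if SD 5 is optimistic, a possibility that the plan leaves open by enrolling 200 partly because the literature is thin: about 72% against 91% at r = 0.5, and 90% against 98% at r = 0.7. The 6–7% type I error is a ceiling that requires free choice of the smaller p-value; the article neither describes that practice nor rules it out.

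**What to change.** Name one primary analysis: ANCOVA of the post-treatment hyperactivity–noncompliance score on arm, baseline score, age stratum and IQ stratum, reporting the adjusted mean difference with its 95% confidence interval. Keep the Mann-Whitney test only as a labelled sensitivity analysis.

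Use the same model for secondary outcomes at post-treatment. For the six-month assessment, adjust for the baseline score taken before randomisation, not for the post-treatment score. The latter is affected by treatment, and conditioning on it would give up the randomised comparison.

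The cost is one paragraph of analysis text and no new data. It should be settled before outcome data by arm are seen.

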### Recruitment

Recruitment will occur among 6 French clinical genetic, psychiatric, or neurologic departments of public hospitals. Detailed oral and written information about the study will be given to the child and their parents by the investigator. For ethical reasons, parents will be informed that children allocated to the motor skill and video viewing intervention could benefit from the «COGNITUS & MOI» program at the end of the study. Inclusion and exclusion criteria will be carefully verified by medical investigators. Parents will give written informed consent, and children will provide oral consent before inclusion in the research program.

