### Randomization

Four strata will be constructed based on age (6–9 and 10–13 years) and total Intellectual Quotient (IQ) score (45–55 and 56–70) to balance characteristics between the treatment groups. After the inclusion of a child, randomization will be done by the statistician involved in the research project and provided to each therapist. The participants and their parents will rate several measures – including primary outcome measures – and will be informed of their group assignment. However, the psychologist will blindly assess the participant’s behavior, cognitive abilities and functional outcomes at baseline, post-treatment, and the 6-month follow-up.

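### The primary test treats all children as independent although therapists shape the experimental treatment; if therapists are nested in arm or differ in delivering COGNITUS, its standard error is too small.

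*Protocol article*

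**What the plan says.** The Statistical analysis section of the protocol article fixes the primary comparison: "Second, independent-sample t-tests or non-parametric Mann-Whitney tests will be run to compare the" change in the ABC hyperactivity–noncompliance score from baseline to post-treatment between the groups. Similar tests follow for every secondary outcome. Neither therapist nor centre enters any of them.

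Other sections describe how treatment reaches the child:

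- More than one therapist is involved. Under Randomization, "randomization will be done by the statistician involved in the research project and provided to each therapist".
- Under The «COGNITUS & MOI» program, each child has 17 meetings with a specially trained therapist, who agrees concrete aims with the family, coaches, and chooses the computer exercises. On the other tasks: "The therapist creates paper-and-pencil activities on a case-by-case basis".
- In the control intervention the activities are set beforehand. The therapist adapts only their difficulty and does not coach beyond reinforcement and session structure.
- The Discussion credits therapeutic alliance with a significant share of the effect of any behavioural therapy.
- On sites, the Recruitment section says "Recruitment will occur among 6 French clinical genetic, psychiatric, or neurologic departments of public hospitals". The randomisation strata are age and IQ only.

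The Sample size section makes no allowance for clustering. It attributes the increase from 126 to 200 to sparse literature and dropout.

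**The concern.** The t-test and the Mann-Whitney test both take each child as a separate piece of information. If a therapist's skill, style or choice of goals moves the outcomes of all the children he or she treats in the same direction, those children carry less information than their number suggests. Where that shared movement differs between arms, it adds to the variance of the treatment contrast, and the planned tests do not see it. The reported interval is then too narrow and the 5% test rejects a true null hypothesis more than 5% of the time.

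The protocol gives its own reasons to expect this. It presents the therapist as an active part of the experimental programme and treats alliance as influential. The primary comparison, and every secondary one made the same way, would be affected. The test is named in the article, so this is a stated choice and not a detail left open for an analysis plan.

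**Working it through.** **The plan's own figure.** Inputs from the Sample size section: "the difference between the two treatments would be at least 3 points"; SD 5; power 90%; two-sided 5%; 1:1 allocation. The normal formula gives 2 × [5 × (1.960 + 1.282)/3]² = 58.4, so 59 per arm (118). The exact t-test gives 60 per arm (120). Scaling 60 by π/3, the usual Mann-Whitney allowance, gives 62.8, so 63 per arm, which matches "a total sample of 126 participants is required". The article does not say that this was the route. None of these calculations contains a clustering term.

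**Assumptions.** The number of therapists, the ICC and whether a therapist treats both arms are not stated. I use 6 or 12 therapists per arm, ICC 0.02, 0.05 and 0.10, and 100 children per arm, all analysed. Six corresponds to one therapist per recruiting department and is an assumption only.

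**Formulas.** With k therapists in an arm, m = 100/k children each.

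- Clustered arm: DE = 1 + (m − 1) × ICC.
- COGNITUS arm only: variance inflation V = (DE + 1)/2.
- Separate therapists in each arm: V = DE.
- True error of the unadjusted test: 2 × [1 − Φ(1.96/√V)].

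Example, k = 6, ICC 0.05: m = 16.7 and DE = 1 + 15.7 × 0.05 = 1.78. In the COGNITUS arm only, V = 2.78/2 = 1.39, √V = 1.18, 1.96/1.18 = 1.66, error 9.7%.

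| Structure | k | V at ICC 0.02 / 0.05 / 0.10 | True error |
|---|---|---|---|
| COGNITUS arm only | 6 | 1.16 / 1.39 / 1.78 | 6.8% / 9.7% / 14.2% |
| COGNITUS arm only | 12 | 1.07 / 1.18 / 1.37 | 5.9% / 7.2% / 9.4% |
| Separate therapists in each arm | 6 per arm | 1.31 / 1.78 / 2.57 | 8.7% / 14.2% / 22.1% |
| Separate therapists in each arm | 12 per arm | 1.15 / 1.37 / 1.73 | 6.7% / 9.4% / 13.7% |

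Simulation with 20,000 trials per setting agrees closely (for instance 9.7% and 14.3% for the two k = 6 rows at ICC 0.05).

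**Same therapists in both arms.** With balanced allocation and a therapist effect common to both arms, the simulated error for 6 therapists is 4.6% / 4.7% / 4.0%: no inflation. If a COGNITUS-specific therapist effect is added to a common effect of 5% of the variance, inflation returns. With a specific share of 0.02 or 0.05, the error is about 6.5% or 9% with 6 therapists, and about 5.3% or 6.9% with 12.

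**Width after adjustment.** Take k = 6, COGNITUS arm only, ICC 0.05. The variances of the two arm means are 0.25 × 1.783 = 0.446 and 0.25. Satterthwaite df = (0.446 + 0.25)²/(0.446²/5 + 0.25²/99) ≈ 12, so t = 2.18 against 1.97 for 198 df. The width ratio is 1.18 × 2.18/1.97 ≈ 1.30. With 6 separate therapists per arm (10 df, t = 2.23) it is 1.335 × 2.23/1.97 ≈ 1.51.

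**Power for 3 points with 200 analysed.** By the normal approximation at 200/DE effective children, 6 separate therapists per arm give 96% / 89% / 75%, and 12 per arm give 98% / 95% / 90%. Using t with 10 df lowers the k = 6 values to about 92% / 82% / 67%. For 6 therapists in the COGNITUS arm only, at ICC 0.05, the t-based value is about 91%.

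**The case against.** The strongest objection is that the facts that decide the matter are not in the document. A reader might infer that the primary test is certainly anti-conservative, or that six departments mean six therapists. Neither is supported. Six counts recruiting sites, and nothing excludes a design in which the same therapists treat both arms, where a common therapist effect cancels. This stands, and it is why the point is conditional. It does not remove the point, because the benign case also needs therapists not to differ in how well they deliver COGNITUS, and the article gives no ground for assuming that.

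It can also be said that tailoring to the child does not in itself make one therapist's children alike, and that common training and a fixed session structure favour uniform delivery. The control therapist also adapts difficulty, and alliance would be expected in both arms. These arguments stand as reasons why the ICC may be small and the contrast between arms less sharp. The primary outcome is parent-rated, which points the same way, although parents share in goal-setting and receive the home-activity instructions. At ICC 0.02 with clustering in the COGNITUS arm only, the error is 5.9% to 6.8%, a modest departure.

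Finally, a reader might infer that leaving out centre also narrows the error bars. It does not: children are randomised individually, so omitting a centre main effect costs precision only.

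**Conclusion.** The concern holds in conditional form. The planned tests assume independence that the described delivery makes doubtful. They give too small a standard error if therapists are nested in arm or differ in delivering COGNITUS, and no inflation under balanced shared therapists with only a common effect.

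The size rests wholly on assumed therapist numbers and ICCs: a true error of about 6% to 14% with clustering in the COGNITUS arm only and 6 or 12 therapists, and about 9% to 22% with 6 separate therapists in each arm. More therapists or a near-zero ICC would make it small. The documents do not support a single figure or an unconditional claim of inflation.

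The main exposure is the error rate and the interval. The planned 200 leaves reasonable power over most of the assumed range, the exception being few therapists with a high ICC. It is worth correcting because it bears on the primary test, and because a therapist identity that was never recorded may not be recoverable later.

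**What to change.** 1. Record a therapist identifier for every child.
2. State how many therapists there are and whether each treats one arm or both.
3. Analyse the primary outcome with a mixed model that has a random therapist effect, arm-specific if therapists are nested in arm or therapist-by-arm if they treat both, and a small-sample degrees-of-freedom correction.
4. Centre may be added as a fixed effect, for precision only.

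The cost is analysis wording and one data field; no extra enrolment or procedures are needed. The statistical price is not negligible if clustering is real: the interval is about 30% wider with 6 therapists in the COGNITUS arm only at ICC 0.05, and about 50% wider with 6 separate therapists per arm at the same ICC. With few therapists the therapist variance is also estimated imprecisely, so the model should be fixed in advance and not chosen according to whether that variance looks important.
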